#### Sample size

A sample size of 30 patients was determined from statistical analysis of the proposed trial. This is sufficient to detect a decrease in repositioning time of at least 10 min with a power of over 95%. An estimated 10-min improvement was identified via a preliminary unpublished volunteer study. This was determined to be the optimal route to estimate the approximate magnitude of time saving before the device was trialled on patients as part of the proposed clinical study.

Power calculations were carried out using Monte Carlo sampling to allow for variability in the number of repositionings per proned session and the number of proned sessions per patient. In addition to standard deviation assumptions, 2–4 repositionings per proning session were used (randomly sampled with proportions (1/5, 3/10, 1/2)) and a dropout rate of 1/3 after the first session. The repeated measurements for each patient were simulated using a correlation of 0.7 within the same treatment and 0.3 between the two treatments.

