### Where patients are proned more than once

If a senior ICU clinician decides that more than one episode of proning is clinically indicated, the method of repositioning will alternate during each subsequent proning session as illustrated below. This illustration is intended for explanation only, and it should be highlighted that the number of times participants in the study are proned will be based solely on clinical indication and decision-making.

If proning is re-employed later in the patient’s ICU stay, the process of alternating the repositioning system will resume. For example, if a patient is proned on day 1 of their ICU admission and is randomised to standard care, and next requires proning on day 5 of the ICU stay, they will be repositioned using the BathMat on day 5, as per the table below.

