### Statistical analysis

We will test for a treatment effect using a linear mixed effects model with repositioning time as the response, fixed effects for site, sequence group assignment, and repositioning method, with random effects for individual to account for repeated measures. Analysis of the number of staff needed to carry out the repositioning procedures will take a similar approach, using a mixed effects cumulative logistic model to account for the discrete nature of the data. All tests will use the conventional 5% significance level.

No imputation or other statistical adjustments for missing data will be undertaken for these analyses. All recorded measurements of repositioning time and the number of staff needed within each proning session for the analysis, which means there is a very low chance that patients will be excluded from the analysis based on missing data. It will not be possible to tell if data on a repositioning exercise is fully missing. Whilst estimates of the treatment effect stratified by case complexity and BMI would be of interest, no sub-group analyses are planned as these would not be statistically reliable given the size of the trial.

This trial is focused on establishing efficacy in relation to the core repositioning outcome. Demonstrating efficacy is a necessary step before progressing to a larger trial that could robustly assess clinical outcomes, such as the prevention of pressure ulcers, which are relatively rare and require significantly larger sample sizes to detect with confidence. As such, this study is not powered to detect statistically significant effects in secondary outcomes, and formal hypothesis testing for these could be misleading. However, collecting and reporting detailed summary statistics will allow assessment of trends, variability, and effect sizes, which are essential for designing an appropriately powered future trial.

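### The crossover model adjusts for sequence but has no term for session number, so change between a patient's sessions can shift the treatment estimate when the two sequences complete unequally; adding the term is a cheap improvement

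*Protocol article*

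**What the plan says.** The Statistical analysis section of the protocol article specifies a linear mixed model for repositioning time with "fixed effects for site, sequence group assignment, and repositioning method", "with random effects for individual to account for repeated measures". For staff numbers it says: "Analysis of the number of staff needed to carry out the repositioning procedures will take a similar approach". No session, period or day term appears in either model, and no sensitivity analysis for period is given.

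The method alternates from one proning session to the next. How many sessions a patient has depends on clinical need, and sessions may be days apart: the section on repeated proning describes a patient who is proned on day 1 and "next requires proning on day 5 of the ICU stay". The Sample size section assumes "a dropout rate of 1/3 after the first session" and lists no period effect among the simulation inputs.

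**The concern.** In this design a patient's method and session are tied together: whichever method comes second is used later in the illness. If repositioning becomes quicker or slower between sessions, the later method gets the credit or the blame. Randomising the order makes the two directions cancel, but only to the extent that both orders supply second sessions in similar numbers.

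The sequence term does not do this job. It is a between-patient factor recording which method came first, and randomisation makes its expected effect nil. Session number is the within-patient factor that would absorb the change, and it is the one left out. Study procedures says that the crossover handles differences between patients; it does not address change within a patient over time.

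What is at stake is the size of the time saving and its interval. These matter because the protocol says its findings will inform performance claims and regulatory planning.

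**Working it through.** **Inputs from the protocol.** 30 patients, 1:1 allocation (taken as 15 per sequence); one third stop after session 1; 2, 3 or 4 repositionings per session with proportions 1/5, 3/10 and 1/2; correlation 0.7 within a method and 0.3 between methods; 10-min target effect.

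**Assumed, because not given.** SD of repositioning time 10 to 20 min; shift between sessions 0, 2, 5 or 10 min.

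**The plan's own figure.** The stated power is over 95% for 10 min. It cannot be reproduced exactly without the SD. Simulating 400 trials per setting with patient and patient-by-method random effects, which match the protocol's two correlations, gives 98.3% at SD 12 and 92.7% at SD 14. The figure is attainable.

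**Step 1: how often the sequences complete unequally.** Completers per sequence follow Binomial(15, 2/3). The SD of the difference is √(2 × 15 × 2/3 × 1/3) = 2.58. P(equal numbers) = 0.15; P(gap of 4 or more) = 0.174.

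**Step 2: shift of the estimate for a given split.** Generalised least squares, 3 exercises per session, 20 two-session and 10 one-session patients. V (in SD² units) = 0.3 for every pair of measurements in a patient, plus 0.4 for pairs under the same method, plus 0.3 on the diagonal. With z the later-session indicator, the shift is the method element of (X′V⁻¹X)⁻¹X′V⁻¹z multiplied by the trend.

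| Completers | Shift, 5-min trend, no session term | Shift with session term | SE without → with term (SD units) | SE cost |
|---|---|---|---|---|
| 10 / 10 | 0 | 0 | 0.2116 → 0.2116 | 0% |
| 12 / 8 | 0.775 min | 0 | 0.2124 → 0.2150 | 1.2% |
| 13 / 7 | 1.176 min | 0 | 0.2134 → 0.2195 | 2.9% |

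Against the 10-min target these shifts are 8% and 12%. They scale with the trend: at 2 min, 0.775 × 2/5 = 0.3 min and 1.176 × 2/5 = 0.5 min.

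**Step 3: effect on the overall error.** Per unit of gap, 0.775/5/4 = 0.0387 of the trend leaks into the estimate. At one SD of the gap that is 0.0387 × 2.58 = 0.10. The error is therefore multiplied by about √(1 + (0.10 × trend)² / (0.2116 × SD)²):

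- 2 min, SD 10: √(1 + 0.04/4.48) = 1.004
- 5 min, SD 10: √(1 + 0.25/4.48) = 1.03
- 5 min, SD 12: √(1 + 0.25/6.45) = 1.02
- 10 min, SD 12: √(1 + 1.00/6.45) = 1.07 to 1.08
- 10 min, SD 10: √(1 + 1.00/4.48) = 1.11

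**Step 4: simulation check** (SD 12, true effect −10, 15:15, at most two sessions, patient and patient-by-method random effects).

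| Later sessions faster by | Session term | Mean estimate | Empirical SD | Power |
|---|---|---|---|---|
| 0 | no | −10.06 | 2.63 | 98.3% |
| 0 | yes | −10.07 | 2.64 | 98.0% |
| 5 min | no | −10.06 | 2.67 | 98.3% |
| 5 min | yes | −10.07 | 2.64 | 98.0% |
| 10 min | no | −10.07 | 2.82 | 97.3% |
| 10 min | yes | −10.07 | 2.64 | 98.0% |

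The mean estimate does not move, so there is no systematic bias. The loss is in the spread: 2.82/2.63 = 1.07 at 10 min, close to Step 3.

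**The case against.** The strongest reply is that the harm rests on a trend nobody has stated. No passage says that repositioning gets faster or slower over a patient's sessions, and at 2 min the loss is negligible. That stands; the figures above are a range, not a prediction.

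A reader might infer a systematic bias. The documents do not support that: allocation is 1:1 and blocked by site, and a single dropout rate is assumed, so the trend cancels in expectation. Average shifts of 1 to 2 min appeared only when the simulation was forced to 18:12 sequences or to dropout of 1/6 against 1/2, neither of which the protocol plans.

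A reader might also infer a 12% larger standard error. With SD 10, a 5-min trend raises the second moment of one completer's difference from 98 to 98 + 25 = 123, and √(123/98) = 1.12. But the trend enters with opposite signs in the two sequences and largely cancels in the trial estimate, whose actual error rises by about 3%.

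Two further points stand. Patients with three or more alternating sessions offset part of a trend within themselves: when up to five sessions are simulated, a 10-min shift raises the empirical SD only from 2.47 to 2.58, about 4%. And session number does not capture a unit's growing familiarity with the device across successive patients, so the argument covers change within a patient only.

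The reply does not remove the core: the fixed effects are listed explicitly, sequence does not substitute for period, and equal completion is expected in only about 15% of trials.

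**Conclusion.** The point holds as a cheap improvement. The stated model leaves chance imbalance in completion free to move the estimate: about 0.8 min at 12 against 8 and 1.2 min at 13 against 7 for an assumed 5-min trend, in either direction depending on which sequence completes more often. Averaged over possible trials with at most two sessions per patient, error rises roughly 2–3% at 5 min (SD 10), 8–11% at 10 min (SD 12 to 10), and is essentially unchanged at 2 min. These figures rest on the protocol's correlations and dropout rate, on 15 patients per sequence, on dropout unrelated to sequence, and on trend and SD values that the protocol does not give. At a true 10-min effect with SD 12 the significance test is hardly affected, so the omission is unlikely to change whether the trial finds a difference. It affects how accurately the difference is estimated.

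**What to change.** Add session number (1, 2, 3 or later) as a fixed effect in the repositioning-time model and in the staff-number model; these are the two models that the section specifies. No new data are needed, because each exercise is already timed and linked to the participant, and session order is already checked against the planned sequence. The cost is one or two degrees of freedom and about 0–1% in standard error at typical balance, about 3% at 13 against 7. The change should be recorded before the data are analysed.

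### The primary model's only stated random part is the patient, which as a random intercept cannot carry the planned 0.7/0.3 correlations; its 5% test then has about 28% type I error

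*Protocol article*

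**What the plan says.** Protocol article, Statistical analysis: the treatment effect is tested in a "linear mixed effects model with repositioning time as the response, fixed effects for site, sequence group assignment, and repositioning method". For the random part, the section gives only this: "with random effects for individual to account for repeated measures". The individual is the only grouping level named. There is no session term, patient-by-method term, structured covariance or robust standard error. The number of staff is to be analysed in a similar way with a mixed cumulative logistic model. "All tests will use the conventional 5% significance level".

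Protocol article, Sample size: a Monte Carlo calculation for 30 patients gave power above 95% for a 10-minute decrease. Repeated measurements were "simulated using a correlation of 0.7 within the same treatment and 0.3 between the two treatments". Each session had 2, 3 or 4 repositionings with probabilities 1/5, 3/10 and 1/2, and there was "a dropout rate of 1/3 after the first session". SD assumptions are mentioned but no value is printed.

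Protocol article, Study procedures: one method is used for a whole session, and the method alternates from session to session.

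**The concern.** A random intercept for the patient makes every pair of that patient's exercises equally correlated, whichever method was used. The planners assumed otherwise. On their figures, 0.7 − 0.3 = 40% of the variance is shared by exercises under the same method but not across methods. Because the method is fixed within a session, that part falls directly on the treatment contrast, and more exercises in the same session do not average it away. An intercept-only model nevertheless counts the 2–4 exercises in a session as nearly independent evidence about the method.

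At stake are the p-value and confidence interval for repositioning time, the response named in the model. The same structure would carry over to the analysis of number of staff.

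**Working it through.** **The plan's own figure.** Power above 95% for 10 minutes cannot be reproduced, because the SD is not given. The type I error can be checked, because it does not depend on the SD.

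**Inputs from the article.** 30 patients; correlations 0.7 and 0.3; 2/3/4 exercises per session with probabilities 0.2/0.3/0.5, so the mean is m = 0.4 + 0.9 + 2.0 = 3.3; one third with one session only, which leaves 30 × 2/3 = 20 patients with both methods; alternating sessions; four sites (the stated minimum). Assumption: two-sided 5% test.

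**Variance split (total variance 1).** Patient 0.3; patient-by-method 0.7 − 0.3 = 0.4; residual 1 − 0.7 = 0.3.

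**Closed form, two sessions of m = 3.3 exercises.**
- True variance of a patient's method contrast: 2(0.4 + 0.3/3.3) = 0.982.
- Residual variance that an intercept-only model pools: [(m/2) × 0.982 + 2(m − 1) × 0.3]/(2m − 1) = (1.62 + 1.38)/5.6 = 0.536.
- Variance of the contrast that this model reports: 2 × 0.536/3.3 = 0.325.
- Ratio of reported to true SE: √(0.325/0.982) = 0.575.
- Type I error: P(|Z| > 1.96 × 0.575) = P(|Z| > 1.127) ≈ 26%.

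**Simulation under the null.** REML with fixed effects for site, sequence and method, and a patient random intercept only:

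| Sessions per patient | Trials | Wald z | t, 18 df |
|---|---|---|---|
| At most two, 1/3 stop after the first | 6,000 | 28.1% | 24.8% |
| Two, no dropout | 1,500 | 27.0% | 23.9% |
| Up to five, 1/3 stop after each | 1,000 | 42.6% | 39.4% |
| 1/3 stop after the first, the rest have 2–5 | 1,000 | 43.6% | 40.0% |
| Up to five, extra correlation by session instead of by treatment | 1,000 | 24.7% | 22.4% |

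In the first row the estimate had an actual SD of 0.221 against a mean model SE of 0.121. The SE is therefore 1 − 0.121/0.221 = 45% too small. The Monte Carlo error of the 28.1% is about 0.6 points.

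**With a patient-by-method random effect added.** Type I error was 6.5% (Wald) or 4.9% (t, 18 df) with at most two sessions (1,500 trials), and 7.0% or 5.4% with up to five (1,000 trials).

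**Session within patient instead of patient-by-method.** The two terms coincide only with at most two sessions. In simulations of 400 trials with up to five sessions and the 0.7/0.3 by-treatment structure, session within patient alone still gave about 19–20%. Patient-by-method gave about 7–10% (Wald), and about 5% with t on 18 df.

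**Power, conditional on an assumed SD.** With the correct variance, SE = SD × √(0.982/20) = 0.2216 × SD. Power of 95% needs SD ≤ 10/[0.2216 × (1.96 + 1.645)] = 12.5 minutes.

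| Assumed SD (min) | Approximation | Simulation, patient-by-method included | Simulation, intercept only (apparent) |
|---|---|---|---|
| 12 | 96% | 98% | 99% |
| 15 | 85% | 89% | 97% |
| 20 | 62% | 68% | 90% |

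The approximation uses only the 20 patients with both methods.

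**The case against.** The strongest objection concerns wording. The article says random effects, in the plural, and never uses the word intercept. An individual-level effect of method would fit that phrase and is essentially the remedy. Planners who simulated separate within- and between-treatment correlations may well have had it in mind, and an unseen SAP may state it. This stands as a condition on the result. It does not remove the point: the article states the random part of its headline model, names only the individual, and beside it gives a covariance assumption that the usual reading cannot represent. That is more than a detail left to the SAP.

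A reader might infer that the stated power is wrong. The documents do not support that. The Sample size section says how data were generated, not which model was fitted, and gives no SD. The SDs of 12, 15 and 20 minutes are assumptions made here, and nothing in the article shows that the true SD exceeds 12–13 minutes.

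It can also be said that an exact null is unlikely, since the Background section expects 30–60 minutes to fall to 10. That is fair for the false-positive risk. It does not help the interval: the SE is too small at any true effect, so a nominal 95% interval would cover about 100 − 28 = 72%.

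**Conclusion.** The point holds, conditionally. If the random part is a patient random intercept and the plan's correlations are right, the SE of the treatment effect is about 45% too small. The 5% test then has about 28% type I error with at most two sessions per patient. Across the readings tried, the Wald test gives roughly 25–44%, depending on the number of sessions and on whether the extra correlation belongs to treatment or session; t on 18 df lowers this only to about 22–40%. If a patient-level effect of method was intended, the error is about 5–7% and only the wording is at fault.

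It would go too far to say that the planned test certainly has 28% error, since the text does not exclude that second reading. Power above 95% for 10 minutes holds under the correct variance only if the SD is about 12–13 minutes or less; whether it is cannot be told from the article. No error rate was computed for the number-of-staff model.

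**What to change.** - State the random part as a patient random intercept plus a patient-by-method random effect. If patients have more than two sessions, add a session-within-patient term to these; do not use it in place of patient-by-method.
- Use Satterthwaite or Kenward-Roger degrees of freedom for repositioning time.
- Use the same random structure in the cumulative logistic model for number of staff.
- Confirm that the power simulation fitted this model and state the SD used. If it did not, rerun it and restate the power.

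The cost is a line or two of wording and, if needed, a simulation rerun. Recruitment is expected to finish around July 2026, so the change should be fixed before the data are analysed. The downside is wider intervals and possibly a less favourable stated power.

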Repositioning is currently typically carried out in one of four ways:The patient is slid up the bed to allow their supported head (now clear of the mattress) to be rotated before returning to the original position. This is the most common method in the UK [4] and is recommended in national and international guidance. It requires at least 5 staff and is associated with a significant manual handling exercise.A hoist can be used to lift the patient off the bed to allow repositioning whilst elevated. Hoists are large devices that require 3–5 staff to operate, they can be difficult to manoeuvre and are typically limited in number on an ICU. This approach requires the insertion/removal of slings, takes approximately the same amount of time as a manual turn described above, and can lead to unpredictable movement of the patient whilst suspended.A specialist proning bed can be used. This is prohibitively expensive (£800+ per day), complicated, and requires large areas for storage when not in use. This approach requires a specialist bed per patient, thereby limiting the number of patients that can be simultaneously proned on any given ICU. This approach is the least preferred and least used repositioning method.Patients can be lifted by staff on the sheet on which they lie whilst one individual turns the head. This requires at least 5 members of staff and is exceptionally demanding from a manual handling perspective, particularly if patients are obese.

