This has led to the development of the inflatable prone repositioning device (IPRD) known as the ‘BathMat’ that is intended to improve the safety and ease of repositioning patients whilst reducing the number of staff and the time required. The BathMat consists of a multi-vessel inflatable pillow, placed underneath a proned patient, which can be inflated to raise the patient’s chest and hips. With the patient raised, repositioning of the head and arms can occur with ease, before the device is deflated and the patient is returned to the resting position. The BathMat has four main benefits for patients and staff:Repositioning of the head and arms occurs without the risks described above.It reduces the number of staff required from 5 to 2.It reduces the time it takes for repositioning from 30–60 min to 10 min.It removes the majority of the manual handling workload.

This study is required to demonstrate the effectiveness of this device in the clinical setting and provide data regarding its safety, usability, and reliability.

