### Objectives and outcomes

See Table 1.

**Table 1 Tab1:** Objectives and outcome measures

Objective	Outcome measure	Source
Primary objective To investigate the staff time required to perform a proned patient reposition exercise. This will include the total number of staff required as well as the duration of the exercise	a. Difference in number of staff required to reposition each patient b. Difference in time required to reposition each patient	The number of staff required to reposition the patient and the time required will be collected by clinical teams by scanning a quick response (QR) code unique to each patient every time a patient is repositioned
Secondary objectives a. Assessment of the number of repositioning exercises undertaken for each patient within a proning intervention b. The number of minor or major adverse incidents associated with repositioning patients whilst in the prone position. This includes events such as line or tube displacement c. The manual handling requirement to reposition d. In patients who suffered a major or minor adverse event (as defined in secondary outcome b), assessment of the healthcare costs relating to that event at 3 months following ICU discharge	a. Number of documented repositioning exercises b. Adverse events documented c. Difference in Likert scale measure of difficulty of repositioning between control and intervention groups d. Healthcare costs of adverse event at 3 months post discharge	a. Clinician form entry from QR code (as above) b. Clinician form entry from QR code (as above), research team form entry c. Clinician form entry (from QR code as above) d. Research team form entry

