### Inflation for repositioning with device

When a patient in the intervention (BathMat) group requires repositioning, the member of staff directly caring for the patient will contact relevant team members to assist with repositioning and prepare the patient. For repositioning with the device, a total of two members of staff are expected to be required. If more are used, the reason for this will be documented on the online form by the clinical team.

Once the patient is prepared, one suitably trained member of staff will control the patient’s head and airway, with a second team member using the control device. Inflation of individual vessels is controlled by the buttons on the control device, as seen in Fig. 4. Upwards arrows inflate the vessels, and downwards arrows deflate the vessels. Inflation is complete when the team assess the patient to be adequately lifted to allow repositioning. The maximum pressure that can be achieved in the vessel corresponds to the input pressure, and the vessel will stop inflating if this maximum pressure is achieved. Following rotation of the head, the device is fully deflated. The patient’s arms are moved when the patient has been returned to rest on the bed. Arm positioning is determined by standard unit protocols. The BathMat must always be left fully deflated in between repositioning sessions.

Repositioning in both groups must be performed every 2–4 h as per Intensive Care Society guidelines. At each point that this frequency is not achieved, the reasoning will be documented by the clinical team using the online data entry form, and will be recorded by the research team.

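### If staffing follows the protocol's own figures, the cumulative logistic model for staff number has no finite odds ratio, and even a finite one would not give the change in staff count that Table 1 asks for

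*Protocol article*

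**What the plan says.** Under the primary objective, Table 1 (Objectives and outcomes) lists two measures. The first is "Difference in number of staff required to reposition each patient"; the second is the matching difference in time.

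The Statistical analysis section gives repositioning time a linear mixed model with "fixed effects for site, sequence group assignment, and repositioning method, with random effects for individual to account for repeated measures". Staff number is to be handled in a similar way, "using a mixed effects cumulative logistic model to account for the discrete nature of the data". It adds: "All tests will use the conventional 5% significance level". It does not say whether the test is Wald or likelihood-ratio.

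The expected staffing is stated in several places:

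- **BathMat.** Background and rationale claims for the device: "It reduces the number of staff required from 5 to 2". Inflation for repositioning with device says that "a total of two members of staff are expected to be required", and continues: "If more are used, the reason for this will be documented on the online form by the clinical team".
- **Standard care.** Of the most common UK method, Background and rationale says: "It requires at least 5 staff and is associated with a significant manual handling exercise". The same section puts a hoist at 3–5 staff. Decision to prone and randomisation, and Repositioning during standard care, leave the method to local practice.

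**The concern.** A cumulative logistic model estimates a finite treatment odds ratio only if the two arms' counts overlap. The protocol's central expectation, two staff against five or more, has no overlap. The better the device performs, the more likely the named model is to return an odds ratio that runs off to infinity with a meaningless standard error.

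Staff number would then have no model-based effect size, or the method would be changed after the data were seen, for a measure listed under the primary objective.

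A second problem does not depend on overlap. The model's effect is a ratio of cumulative odds, whereas Table 1 asks for a change in the number of staff. A performance claim about how many staff are released needs the latter.

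**Working it through.** The plan states no power or precision for staff number, so there is no figure of its own to reproduce. The power of over 95% in Sample size concerns a 10-minute fall in time.

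**1. Number of BathMat repositionings.** Sample size gives 30 patients, 2, 3 or 4 repositionings per session with proportions 1/5, 3/10 and 1/2, and a dropout of 1/3 after the first session. Two sessions at most are assumed here.

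- Mean per session: 2×0.2 + 3×0.3 + 4×0.5 = 3.3.
- BathMat repositionings: 15×3.3 (BathMat first) + 15×(2/3)×3.3 (BathMat second) = 49.5 + 33 = 82.5, taken as 82.

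**2. Does the planned model have a maximum?** The model is P(Y ≤ k) = F(θ_k − η), where η holds site, sequence, method coefficient β and patient intercept. If the largest BathMat count is no greater than the smallest standard-care count, β can fall without limit, with the lower thresholds moving along, and the likelihood never drops. Patient intercepts do not alter this.

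One trial of the protocol's size was simulated per scenario and the mixed model fitted by quadrature, with the log-likelihood profiled over β:

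| BathMat / standard staff | β = 0 | −4 | −8 | −14 | −20 | LR statistic (1 df) | Mean difference |
|---|---|---|---|---|---|---|---|
| 2 / 5–7 | −188.3 | −94.5 | −75.9 | −72.2 | −72.0 | 232 | −3.5 |
| 2–5 / 5–7 (touch at 5) | −241.4 | −159.2 | −147.3 | −146.739 | −146.738 | 189 | −3.2 |
| 2 / hoist 3–5 | −198.5 | −107.5 | −89.4 | −86.5 | −86.3 | 224 | −2.2 |
| 2–4 / 3–7 (overlap) | −275.4 | −193.0 | −194.7 | −231.6 | −273.6 | 172 | −2.8 |

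In the first three rows the likelihood keeps rising, so there is no finite estimate. This includes hoist staffing against a constant two, and arms that only touch. In the fourth row the maximum is finite, near β = −6 on the grid used. The likelihood-ratio statistic and the mean difference are available in every row.

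**3. How likely is separation?** Let p be the chance that a BathMat repositioning uses more staff than the smallest standard-care team. If repositionings are independent, P(none does) = (1 − p)^82:

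- p = 0.5%: 0.995^82 = 66%
- p = 1%: 0.99^82 = 44%
- p = 2%: 0.98^82 = 19%
- p = 5%: 0.95^82 = 1.5%

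A simulation (400 trials per cell, Monte Carlo standard error at most √(0.25/400) = 0.025) varied the share of BathMat repositionings using more than two staff, the size of those larger teams, and hoist use. Standard care used 5, 6 or 7 staff with probabilities 0.6, 0.3 and 0.1, or that mix with 25% hoist teams of 3–5.

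| Share above two staff | Standard ≥5; larger teams 3–4 | Standard ≥5; larger teams 5–6 | 25% hoist; larger teams 3–4 | 25% hoist; larger teams 5–6 |
|---|---|---|---|---|
| 0 | 1.00 | 1.00 | 1.00 | 1.00 |
| 0.5% | 1.00 | 0.84 | 0.84 | 0.66 |
| 1% | 1.00 | 0.70 | 0.62 | 0.44 |
| 2% | 1.00 | 0.40 | 0.46 | 0.19 |
| 5% | 1.00 | 0.13 | 0.11 | 0.005 |
| 10% | 1.00 | 0.02 | 0.03 | 0.00 |
| 20% | 1.00 | 0.00 | 0.00 | 0.00 |

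The second column exceeds (1 − p)^82 at the same share because a BathMat team of exactly five only touches the standard range and leaves the data separated. The first column is 1.00 by construction, since its ranges cannot overlap.

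**The case against.** A reader might infer that the staff-number measure cannot be estimated at all, or that the model is bound to fail. The documents support neither.

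- **Staffing is not fixed.** Two staff are only expected with the BathMat, and larger teams are foreseen and documented. Standard care is local practice, so hoist teams are possible, and Study setting wants sites with differing practice. This stands: separation is a risk whose size depends on rates the protocol does not give.
- **Inference is not wholly lost.** No Wald test is named. Under separation a likelihood-ratio test is finite and overwhelming, and the raw difference in staff can be read off. This also stands. What is lost is the model's effect estimate and any Wald interval.
- **A fallback may be in the analysis plan.** Handling of non-convergence is commonly left to that document, which is not shown, so its absence here is no fault. But the protocol does name the model, and the mismatch between an odds ratio and Table 1 follows from that choice.
- **Table 1 does not say a difference in means, and an ordinal model for a small count is standard.** This is fair, but no reading of a difference in staff number yields a cumulative odds ratio.
- **An ordinary linear mixed model has its own flaw.** If every BathMat repositioning uses two staff, that arm has no variance and a common residual variance is wrong. This stands and shapes the fix.
- **The stakes are limited.** The Abstract and Data entry by clinical team define the primary outcome as total staff time; staff number is one component of it. This stands and keeps the point below the level of a fatal fault.

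**Conclusion.** The point holds conditionally. At the protocol's own figures the named model has no finite odds ratio and no usable Wald interval for one of the two Table 1 measures under the primary objective. Separation is certain if no BathMat repositioning uses more staff than the smallest standard-care team. It remains likely at exception rates up to about 1%, and becomes unlikely at 5–10% if the larger BathMat teams reach the standard-care range.

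The algebra is firm; the probabilities are illustrative. They assume at most two sessions per patient, independent repositionings, and invented exception rates, team sizes and hoist share. Clustering of exceptions within patients would raise the chance of separation at a given rate; extra BathMat sessions would lower it.

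Whether or not the data separate, the odds ratio is not the quantity Table 1 describes. That alone justifies a change of reported effect.

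**What to change.** In the Statistical analysis section:

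1. Make the mean difference in staff per repositioning, BathMat minus standard care, the reported effect for staff number.
2. Give it an interval and a test that do not rely on equal residual variance in the two arms, for example a randomisation test that permutes sequence within site, or a patient-level bootstrap.
3. Keep the mixed cumulative logistic model as supportive, tested by likelihood ratio, with a penalised fit if the data are separated.

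The cost is a sentence or two, with no new data and no change to trial conduct. The downside is that a small integer count is treated as numeric, which is acceptable because the count itself is what Table 1 compares. The change should be made before the outcome data are examined, so that it does not look like a response to a failed fit.
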